## Abstract

**Background: **Surgical resection remains the primary curative treatment for intra-cavity cancer. Low physical fitness and psychological factors such as depression are predictive of post–operative morbidity, mortality and length of hospital stay. Prolonged post-operative morbidity is associated with persistently elevated risk of premature death. We aim to investigate whether a structured, responsive exercise training programme, a psychological support programme or combined exercise and psychological support, delivered between treatment decision and major intra-cavity surgery for cancer, can reduce length of hospital stay, compared with standard care.

**Methods: **WesFit is a pragmatic
**, **2x2 factorial-design, multi-centre, randomised-controlled trial, with planned recruitment of N=1560. Participants will be randomised to one of four groups. Group 1 (control) will receive usual pre-operative care, Group 2 (exercise) patients will undergo 2/3 aerobic, high-intensity interval training sessions per week supervised by personal trainers. Group 3 (psychological support) patients are offered 1 session per week at a local cancer support centre. Group 4 will receive both exercise and psychological support. All patients undergo baseline and pre-operative cardiopulmonary exercise testing, complete self-report questionnaires and will be followed up at 30 days, 12 weeks and 12 months post-operatively. Primary outcome is post-operative length-of-stay. Secondary outcomes include disability-adjusted survival at 1-year postoperatively, post-operative morbidity, and health-related quality of life. Exploratory investigations include objectively measured changes in physical fitness assessed by cardiopulmonary exercise test, disease-free and overall mortality at 1-year postoperatively, longer-term physical activity behaviour change, pre-operative radiological tumour regression, pathological tumour regression, pre and post-operative body composition analysis, health economics analysis and nutritional characterisation and its relationship to post-operative outcome.

**Conclusions: **The WesFit trial will be a randomised controlled study investigating whether a high-intensity exercise training programme +/- psychological intervention results in improvements in clinical and patient reported outcomes in patients undergoing major inter-cavity resection of cancer.

**ClinicalTrials.gov registration: **NCT03509428 (26/04/2018)

## Introduction

The number of new cancer cases per year is expected to rise to 23.6 million by 2030. Depending on the cancer cohort, major curative cancer surgery is associated with post-operative morbidity in up to 50% of gastrointestinal cancer patients and up to 60% in pancreatic cancer patients especially after neoadjuvant cancer treatments.
^
1–
3
^ Improved surgical, oncological and anaesthetic techniques, enhanced recovery pathways and perioperative care have delivered consistent improvements in length of hospital stay, in-hospital morbidity and readmission rates after major surgery. However, over half of patients over the age of 60 years after major abdominal surgery live with reduced functional capacity, physical fitness and quality of life (QoL), with a significant proportion never regaining pre-operative fitness or independent living.
^
4,
5
^ Our group have described the association between reduced pre-operative physical fitness
^
6–
11
^ (and its decline with neoadjuvant cancer treatments) and poor post-operative outcomes in upper and lower gastrointestinal cancer patients. Furthermore, we have reported on the associations between reduced physical fitness and reduced mitochondrial function,
^
12
^ QoL
^
13,
14
^ and physical activity
^
15
^ after cancer treatments before surgery. This is mirrored by others describing the associations of selected objectively measured fitness variables using cardiopulmonary exercise testing (CPET) and postoperative complications and length of hospital stay.
^
16
^ Moreover, a recent systematic review
^
17
^ also shows that higher preoperative physical activity levels were associated with shorted length of hospital stay and better postoperative (QoL), but not reduced postoperative complications. Interestingly, interrogating physical activity time preoperatively showed that patients who were regularly physically active had lower postoperative complications after colorectal surgery.
^
18
^ Although this is all intuitive, clinical trials in this area are heterogenous, provide a mixed picture with elusive pathophysiological explanations.

Cancer prehabilitation is a novel process that occurs between the time of cancer diagnosis and continues throughout the cancer treatment pathway. The time before cancer diagnosis and surgery is an emotionally salient time where patients are receptive to changes in behaviour regarding their nutrition, fitness and psychological coping. Physical fitness, nutritional and psychological multimodal prehabilitation are targeted, tailored interventions with the aim to prevent, minimise and/or rescue the severity of anticipated treatment-related impairments that may cause significant disability when recovering from major cancer surgery.
^
19
^ Given the multi-system impact of cancer and its treatment(s), prehabilitation interventions have adopted a ‘multimodal approach’, that may be defined as the incorporation of two or more intervention components specifically selected for their potential cumulative or synergistic effects on health outcomes. Reviews of prehabilitation in surgical oncology identify many limitations in the current evidence, yet acknowledge encouraging findings including improved fitness, endurance time, length of hospital stay, surgical complication rates, and health-related QoL with prehabilitation interventions.
^
20–
29
^ Recently, multinational consensus statements jointly from Macmillan Cancer Support, the Royal College of Anaesthetists and the National Institute for Health Research in the United Kingdom,
^
30
^ Exercise and Sports Science Australia
^
31,
32
^ and the Academy of Medical Royal Colleges in the United Kingdom
^
33
^ aim to advance the care provision, inform a change in policy, inform service provision, and implement a practice to benefit people living with cancer. Specifically, effective prehabilitation using multimodal physical activity, exercise, nutrition and psychological support, underpinned by behaviour change support, to improve cancer outcomes is advocated. Thus far the evidence is mostly based on uni-modal interventions, for example exercise interventions to improve physical fitness and post-operative complications
^
23,
25,
34–
37
^ and respiratory interventions to improve pulmonary specific morbidity,
^
29
^ however literature utilising multimodal interventions (mostly exercise and nutrition) to improve outcomes is now emerging.
^
21,
22,
38,
39
^ Recently published high-quality randomised trials in colorectal cancer surgical patients have showed mixed outcomes with Carli
*et al.* (multimodality prehabilitation) unable to improve postoperative outcomes in a cohort of patients aged 65 years and over,
^
40
^ Barberan-Garcia,
^
41
^ (motivational interviews, physical activity programme and supervised high-intensity endurance exercise) improving aerobic capacity and reducing post-operative compilations and Onerup
*et al*.
^
42
^ (home based aerobic activity and inspiratory muscle training) showing no effects on physical recovery or improvement in outcomes.

To date exercise prehabilitation trials have focused on in-hospital training with little consideration for sustainable models of delivery. There has also been a lack of inclusion of behavioural science to facilitate engagement and longer-term behaviour change post-surgery. Furthermore, increasingly, evidence suggests that psychological factors impact physiological and psychological outcomes in both the short and long term, with implications for recovery from surgery, QoL and re-attainment of independent living.
^
43
^ A systematic review of psychological prehabilitation before cancer surgery suggests such interventions can positively impact QoL and psychological outcomes (such as distress and anxiety). However prehabilitation studies including a psychological component have tended to be small, therefore, an evaluation of a psychological intervention together with an exercise intervention as part of a multimodal prehabilitation programme in cancer patients is urgently needed.
^
26
^

## Protocol

### Study design and setting

The Wessex Fit-4 Cancer Surgery trial (WesFit) is a multi-centre, 2 × 2 factorial design, randomised-controlled, single blind, phase III clinical trial designed to compare the effect of structured prehabilitation programmes, against standard pre-operative care on patient outcome following major intra-cavity surgery for cancer (
Figure 1). Participant recruitment, assessment and intervention are organised by NHS Hospital trusts who oversee referral to our community partners in local gymnasiums (exercise and behaviour change intervention) and Cancer Support centres (psychological intervention). The trial was registered with
clinicaltrials.gov (NCT03509428) on April 26th, 2018. This protocol follows the SPIRIT guidelines – see
*Reporting guidelines*.
^
62
^

**Figure 1. f1:**
[figure not shown]
Trial summary diagram. MDT: multidisciplinary team, CPET: cardiopulmonary exercise test, SREPT: structured responsive exercise training programme, WHODAS: World Health Organisation Disability Adjusted Survival.

### Study objectives

Primary objective: investigate whether a multimodal exercise, and psychological support prehabilitation programme, performed in a community-based setting prior to major cancer surgery, (± neoadjuvant cancer treatments) will result in a clinically significant difference (1-day reduction) in post-operative in-hospital length of stay) when compared to a control group.

Secondary objectives: investigate whether the WesFit programme performed prior to major cancer surgery ± neoadjuvant cancer treatments:
i.Improves disability free survival as measured by World Health Organisation (WHO)
Disability Adjusted Survival v2.0
ii.Improves post-operative morbidity
^
44
^ as measured by post-operative morbidity score (POMS) and Clavien-Dindo-Demartines (CD)
^
45
^/comprehensive complication index (CCI) scores
^
46
^
iii.Improves health related QoL as measured by EQ-5D-5L
^
47
^ and EORTC-QLQ-C30.
^
48
^

Exploratory objectives include:
i.Improve overall survival and disease-free at one-year post-surgeryii.Improve selected cardiopulmonary exercise test (CEPT) physiological variablesiii.Improve long-term physical activity behaviouriv.Demonstrate cost effectiveness determined by health economics analysisv.Improve radiological markers of body compositionvi.Improve radiological tumour regression grade (TRG)vii.Improve pathological tumour regression grade (yTRG)viii.Improve psychological outcomes including confidence to self-manage illness, anxiety and depression.ix.Improve body composition measured by computer tomography and bioelectrical impedance analysesx.Improve nutritional and micronutrient status measured by micronutrient blood analysis

### Eligibility criteria

Patients will be eligible for WesFit if they are over 18 years old and are scheduled to have major, intra-cavity cancer surgery with a curative intent. These are defined as thoracic, colorectal (including anal and neuroendocrine tumours), oesophagogastric (including neuroendocrine tumours), urological (including prostate, bladder and renal tumours), head and neck (including nasopharyngeal, laryngeal, pharyngeal and oral) and hepatobiliary (including pancreatic, gall bladder and neuroendocrine tumours). Treatment includes surgery alone or surgery combined with cancer treatments (including but not limited to neoadjuvant chemotherapy, chemoradiotherapy or immunotherapies). All patients deemed by the multidisciplinary team (MDT) as potentially curable or undergoing neoadjuvant cancer treatments with curative intent prior to restaging and surgery will be included.

Exclusion criteria includes patients with a tumour that is considered surgically non-resectable, having absolute or relative contraindications to completing a CPET,
^
49
^ patients unable to perform CPET due to other coexisting acute illness or conditions (e.g. lower limb dysfunction), patients declining surgery or planned neoadjuvant treatment, if their weight exceeds 160 kg and patients unable to give informed consent.

### Recruitment and randomisation

Consecutive, potentially eligible patients will be identified at MDT meetings and approached with patient information sheets at surgical/oncological outpatient clinic appointments. If the patient chooses to participate in this trial, they will undergo a screening CPET. This constitutes part of standard clinical care in some NHS hospitals. Once reviewed by a senior clinician, final eligibility is confirmed, and written informed consent can be obtained for trial participation.

Patients will be randomised 1:1:1:1 to one of four groups. The study design is a 2 x 2 factorial design. The randomisation will be performed using
ALEA
^TM^
 from FormsVision, an online software not under the control of the study team. Patients will be randomised by ALEA
^TM^ by minimisation to the multimodal interventions or the control arm and stratified according to tumour type, hospital site, gender, neoadjuvant cancer therapy and age. Group 1 is control (routine care), group 2 is exercise alone, group 3 is psychological support alone and group 4 is a multimodal exercise, and psychological support.

WesFit began recruitment in April 2018 and at the time of publishing was paused due to coronavirus disease 2019 (COVID-19) lockdown restrictions.

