## Ethics and dissemination

The trial was initially authorised by London – Westminster Research Ethics Committee (REC reference 18/LO/0129) on 06/03/2018. Before a patient is randomised to the WesFit Trial, written informed consent will be obtained. When obtaining consent from a patient, the trial and the patient information sheet will be introduced in full. Written confirmation that the patient has given their consent to participate in the trial will be recorded by member of the research team according to local practice.

**The chief investigator and trial sponsor will have access to the full dataset.** Generalisable results will be published in scientific journals, incorporated into multi-disciplinary society guidelines and presented at cross-disciplinary international scientific conferences, patient groups, cancer charities and NIHR strategic partners.

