## Safety reporting

All adverse events are to be recorded in the relevant case report form. Adverse events during CPET are reported to the chief investigator, and adverse events during exercise training (pain and muscle soreness) or psychological support sessions (mental health concerns) are reported to the trial coordinator by the instructor/counsellor and recorded in the relevant case report form by the research physiologist/nurse. Fatal or life-threatening serious adverse events (SAEs) are reported within 24 hours of the local site becoming aware of the event. The SAE form documents the nature of the event, date of onset, severity, corrective therapies given, outcome and causality (that is, unrelated, unlikely, possibly, probably, or definitely). Questions concerning adverse event reporting are directed to the chief investigator in the first instance.

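### As printed, written consent follows the screening cardiopulmonary exercise test, so at any site where that test is not routine care a trial-specific procedure precedes written consent

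*Protocol article*

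**What the plan says.** The Recruitment and randomisation section sets out a sequence. Potentially eligible patients are identified at multidisciplinary team meetings and are "approached with patient information sheets at surgical/oncological outpatient clinic appointments". Next: "If the patient chooses to participate in this trial, they will undergo a screening CPET". The text then remarks on the test: "This constitutes part of standard clinical care in some NHS hospitals". The sequence closes with: "Once reviewed by a senior clinician, final eligibility is confirmed, and written informed consent can be obtained for trial participation". Randomisation follows.

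The Ethics and dissemination section gives the only other statement on timing: "Before a patient is randomised to the WesFit Trial, written informed consent will be obtained". It adds: "When obtaining consent from a patient, the trial and the patient information sheet will be introduced in full".

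Two further sections show that the protocol treats the test as carrying some risk. Eligibility criteria excludes patients with absolute or relative contraindications to CPET, and Safety reporting gives such events their own route: "Adverse events during CPET are reported to the chief investigator".

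**The concern.** Written consent is normally in place before anything is done to a patient purely for a trial. Here the printed order puts an exercise test first and the signature last. Where the test belongs to the patient's ordinary preoperative work-up, that order does no harm: the test would have happened anyway, and consent then covers the use of its result. Where it does not, the patient exercises on test equipment because of the trial, with nothing signed.

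What is at stake is mainly protection of the patient. There is also a documentation point. If a patient has an event during a screening test done only for the trial, or does not pass the screen, the article does not say under what written permission that information enters the trial record.

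**Working it through.** No arithmetic applies. The check is the order of events, and whether any text places written consent before the test.

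**1. Order in Recruitment and randomisation.**
- Information sheet given at an outpatient clinic.
- Patient chooses to take part.
- Screening CPET.
- Review by a senior clinician.
- Final eligibility confirmed.
- Written consent.
- Randomisation.

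The order is stated in the text; it is not inferred from a silence.

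**2. Why the test is done.** The stated trigger is the patient's decision to join the trial. CPET is described as standard in some hospitals only, which leaves room for others where it is not. The test also serves trial purposes: the Abstract has all patients undergo a baseline CPET, Interventions sets training intensity from the baseline test, and Exploratory outcomes includes oxygen uptake at the anaerobic threshold and at peak. The article does not say in so many words that the screening test and the baseline test are the same one.

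**3. Whether Ethics and dissemination repairs the order.** Consent before randomisation is satisfied by the sequence above, because both the test and the consent precede randomisation. The two sections are therefore compatible, and neither puts consent before the test. The statement that the trial is introduced in full when consent is obtained, read with the sequence, places that full introduction after the CPET, although the information sheet has been given earlier.

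**4. Any other text.** Eligibility criteria, Outcome measures, Safety reporting and the monitoring sections mention no earlier or separate written consent for the screening test.

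**5. Size.** If a share p of randomised patients is screened at sites without routine CPET, then p × 1560 of the planned 1560 have the test before written consent, plus those at such sites who are screened and not randomised. The article gives no value for p and nothing that bounds it, so the result runs from 0 × 1560 = 0 to 1 × 1560 = 1560. That is no estimate, and a narrower range would be a guess.

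**The case against.** The strongest reply is that the article condenses a fuller protocol. A separate written consent for the test may exist there or in the site paperwork, and the phrase about consent for trial participation leaves room for one. The trial also had ethics committee authorisation. Further, the remark about some NHS hospitals describes the health service at large; it does not say that any participating site lacks routine CPET. These points stand as limits on certainty, and they make the finding conditional. They do not remove it: the printed order is explicit, and if a screening consent exists the article describes the consent process wrongly and should say so.

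A reader might infer more than the documents support, in four ways.

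- *That patients are tested without having agreed.* They have received the information sheet and chosen to take part. What the printed sequence lacks at that point is written consent.
- *That patients with contraindications necessarily meet the test before consent.* The exclusions concern contraindications to CPET and inability to perform it. These can be checked beforehand, and nothing says that they are discovered by doing the test.
- *That the Safety reporting section shows screening events in unconsented people being treated as trial events.* CPET is repeated before surgery in all patients, and every four weeks during neoadjuvant treatment where the site can offer it (Outcome measures), so the reporting rule has an obvious use after consent.
- *That screening results or events cannot be kept, so that CPET safety is counted only in those who passed.* No text says this. The Safety reporting section asks for all adverse events to be recorded, screen failures can be counted by reason without identifiable data, and CPET safety is not a listed outcome.

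**Conclusion.** The point holds in a limited, conditional form. As printed, the article places written consent after the screening CPET and requires it only before randomisation. At any participating site where CPET is not routine care, a trial-specific procedure therefore precedes written consent.

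The conclusion rests on two assumptions: that at least one site does not offer CPET routinely, which the article's wording suggests but does not state, and that no separate screening consent exists in documents not shown. The number of patients concerned cannot be given.

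There is no consequence for the estimated treatment effects. Screening comes before allocation, so it cannot bias one arm against another, and power is unaffected. The case for acting is patient protection and a clean consent record.

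**What to change.** - **Recruitment and randomisation:** state that wherever CPET is not part of the patient's routine care, written consent is obtained before the screening CPET. This may be full trial consent or a separate written screening consent. Where CPET is routine, consent may follow, with explicit permission to use the result.
- **Ethics and dissemination:** change the timing from before randomisation to before any trial-specific procedure, so that the two sections agree.
- **Screening record:** enter consented patients who do not pass the CPET screen as screen failures, not randomised, and report any adverse events during their test.
- **If a screening consent already exists:** describe it in both sections. The correction is then one of wording only.

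The cost is an amendment to the protocol and the consent process. Some patients will sign and then not be randomised. The planned 1560, the minimisation and the analysis do not change. Recruitment was paused when the article was published, so from the article's standpoint the change could be made before restart.

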### Interventions

**Exercise intervention:** The exercise-training programme is consistent with the FITT principle (frequency, intensity, time and type), as advised by a panel of international experts and patient representatives. The exercise intervention has been shown by our group to be safe, feasible and tolerable in locally advanced rectal cancer patients following neoadjuvant chemoradiotherapy.
^
34,
45
^ Patients will participate in a prescribed, supervised, aerobic high-intensity interval, structured, responsive, exercise training programme (SRETP) on an electronically-braked cycle ergometer (Ergoselect Cloud bike). Participants will undertake 3-sessions per week (2-sessions per week if undergoing neoadjuvant treatments), from recruitment to surgical resection. These will occur within community gymnasia, unless precluded by safety concerns due to clinical condition. High-risk patients can exercise within a hospital setting. The high-intensity interval training (HIIT) comprises of an initial 5 minutes of unloaded pedalling. This is followed by 3 minutes at moderate intensity and 2 minutes at severe intensity. Moderate intensity exercise refers to the patient’s power output at 80% of oxygen uptake (VO
_2_) at the anaerobic threshold, (80%AT) derived at baseline CPET. Severe exercise intensity occurs at the patient’s power output, at 50% of the difference between the VO
_2_ at AT and VO
_2_ Peak (50%∆) also accounting for 2/3 of the ramp work rate. These 5-minute intervals will be repeated 6 times, followed by 5 minutes of unloaded pedalling. The entire session lasts for 40 minutes. If the patient is receiving neoadjuvant treatment the entire session lasts for 30 minutes, with the 5-minute intervals repeated 4 times rather than 6 times. The full exercise programme is reported according to the Template for Intervention Description and Replication (TIDiER) checklist for exercise. The checklist is available in
*Extended data*.
^
62
^

As part of the exercise intervention personal trainers delivering the supervised exercise intervention will receive training in behaviour change support in the form of Healthy Conversation Skills (HCS). HCS is a brief intervention, developed to equip health and social care practitioners with the skills to support improvements in diet and physical activity in their patients/clients.
^
50
^ Informed by principles of motivational interviewing and social cognitive theory it is an empowering, client-centred, solution-focused approach to support behaviour change. Self-efficacy, a central construct of Bandura’s social cognitive theory,
^
51
^ describes a person’s belief in their abilities to perform a given task. Self-efficacy is also considered to be a prerequisite to an individual experiencing a sense of control. Evidence suggests that self-efficacy is a mediator of exercise behaviour in clinical populations and a predictor of exercise adherence.
^
52
^ See
Table 1 for included behaviour change techniques as per the behaviour change technique taxonomy.
^
53
^ Personal trainers work with participants throughout the intervention to increase motivation, self-efficacy and support planning for continued unsupervised exercise after surgery. Personal trainers have telephone consultations at three and six months after surgery to support long-term engagement in independent physical activity. The behaviour change intervention is reported according to the TIDiER checklist in
*Extended data*.
^
62
^

**Table 1. T1:** Behaviour change techniques (BCT) coded to the BCT taxonomy (BCTT V1).

BCT label	BCT no. (BCTT v1)	Example Intervention component
Goal setting (behaviour)	1.1	Participants set goals for independent exercise engagement following surgery.
Problem solving	1.2	Trainers use the SMARTER goal setting sheets to prompt the participant to analyse factors that might get in the way of them achieving a goal and how it can be overcome.
Action planning	1.4	Trainers use SMARTER goal setting sheets to prompt detailed specification of goals including day of the week and time that they will perform a particular behaviour to be performed in the early recovery period after surgery.
Review behaviour goal(s)	1.5	Trainers will review behaviour goal(s) with the participants and modifies them collaboratively as necessary, e.g. setting an easier goal if the previous goal was not achievable.
Feedback on behaviour	2.2	The trainer and participant will reflect and discuss changes to exercise behaviour, particularly when exercising independently after surgery.
Self-monitoring of behaviour	2.3	Participants will be encouraged to keep a diary of their independent exercise.
Social support (unspecified)	3.1	The trainer will provide praise and encouragement throughout the trial.
Instruction on how to perform a behaviour	4.1	The trainer will provide specific instructions during the structured exercise sessions.
Graded tasks	8.7	The trainer will work with participants to start with easy to achieve independent exercise goals, gradually increasing the difficulty overtime.
Credible source	9.1	The trainer presents as a credible source with in-depth understanding of the benefits of exercise following a cancer diagnosis.
Verbal persuasion about capability	15.1	The trainer will reassure participants that the exercise programme is based on their fitness levels and is achievable.
Focus on past success	15.3	The trainer will encourage the participant to review progress made over the course of the trial.

**Psychological support:** Psychological support will be provided in the form of counselling. Counselling will be delivered by counsellors experienced in working with people affected by cancer. Counsellors are members of the British Association of Counselling and Psychotherapy with a minimum qualification of a Diploma in Counselling and Psychotherapy. The processes reflect the best practice currently delivered by cancer support centre staff. Participants will be offered weekly one-to-one consultations lasting up to 1 hour, allowing them to explore any issues/concerns they are experiencing, including (but not limited to) ways of coping with their reaction to cancer, family and relationship issues, anxiety and distress. After each session, counsellors will complete a checklist indicating counselling techniques used. The psychological support intervention is reported according to the TIDiER checklist in
*Extended data*.
^
62
^

Adherence will be monitored throughout the trial. The trial team will receive automatic uploads of exercise adherence from the card- and cloud-based systems and attendance (or not) at counselling sessions will be logged.

**Control group:** The control group will receive routine pre- and post-operative care with additional assessments common to all groups, but no intervention outside of routine care.

